## Abstract

**Background:**

Worldwide, prevalence rates of adolescent non-suicidal self-injury (NSSI) range between 13 and 45%. In Germany, lifetime prevalence of NSSI is around 25% in non-clinical samples, and the one-year prevalence for repetitive NSSI is 4%. NSSI is present in the context of several axis I and II disorders (for example, affective disorders or borderline personality disorder); however, preliminary evidence suggests that it would be justified to consider NSSI as its own diagnostic category. Despite the large impact of this behavior, there is still a lack of evidence-based, specific, and effective manualized treatment approaches for adolescents with NSSI.

**Methods/Design:**

The study is designed as a randomized controlled trial (RCT) to test the effectiveness of a new cognitive-behavioral treatment manual for self-harming adolescents - the ‘Cutting-Down-Programme’ (CDP). A total of 80 adolescents aged between 12 and 17 years from a region in Southern Germany who have engaged in repetitive NSSI (≥5 incidents) in the last 6 months will be randomized into a treatment group (CDP) or a control group that will receive treatment as usual (TAU). The adolescents will be assessed by means of structured interviews and questionnaires at three time points (before treatment, directly after treatment and six months after treatment). Primary outcome criterion is a significant reduction (or remission) in the frequency of NSSI. Secondary outcome criteria are depressivity as well as general well-being and self-worth. Additionally, comorbid psychiatric disorders and childhood adversity will be evaluated as predictors of therapeutic outcome.

**Discussion:**

Recently, a pilot study in the United Kingdom showed significant reductions in self-harming behavior, depressive symptoms and trait anxiety. This is the first RCT to test the effectiveness of a short-term psychotherapeutic intervention in outpatients engaging in NSSI.

**Trial registration:**

The study is registered in the German Clinical Trials Register DRKS00003605.

## Background

Non-suicidal self-injury (NSSI) can be defined as a self-inflicted, deliberate, direct destruction of body tissue without conscious suicidal intent, which is not socially accepted [1,2]. During adolescence, prevalence ranges between 13 and 45% worldwide [1,3,4], and studies in the same population in Germany suggest a similar prevalence [4,5]. In a large school-based, cross-sectional study conducted during 2004/2005 in the defined catchment area (southwestern Germany), 15% of the 15-year-old adolescents included reported NSSI in the previous six months; 4% of them even reported repetitive NSSI [5]. Another study within the same geographical area from 2011 revealed a lifetime prevalence of any incident of NSSI of 35% among 14- to 16-year-old adolescents [6].

NSSI is often accompanied by a variety of psychological problems and disorders, but until recently, borderline personality disorder (BPD) was the only disorder in the classification systems (Diagnostic and Statistical Manual of Mental Disorders-IV (DSM-IV) and International Statistical Classification of Diseases and Related Health Problems-10 (ICD-10) that included self-injury as a diagnostic criterion. NSSI can occur in the context of depressive disorders, eating disorders, anxiety disorders, conduct disorders, substance-use disorders and post-traumatic stress disorders [7,8]. In addition, NSSI is highly associated with suicide attempts and death by suicide in adolescents [5,9]. As a result of increasing knowledge on the phenomenon of NSSI and its growing importance, NSSI has now been included as a section 3 disorder in the new DSM-5 [10-12]. This fact underscores the need for further research concerning NSSI and for the development of specific therapeutic concepts that are empirically validated for the condition.

To our knowledge, specific therapeutic programs focusing specifically on NSSI are rare [10]. The only existing manuals were originally developed for treatment of BPD, and consequently treat NSSI as one symptom of this disorder [13,14]. In this context, the Dialectic Behavioral Therapy for Adolescents (DBT-A) is the most common program [15], but its effectiveness in reducing NSSI has not been proven in a randomized controlled trial (RCT) so far [16]. Additionally, extensive therapeutic approaches like those for BPD may not always be adequate in light of the high prevalence of adolescent NSSI. A new therapeutic approach using mentalization-based therapy (MBT) for self-harming adolescents was recently published by Rossouw and Fonagy. In their RCT, they were able to achieve a recovery rate of 44% in the MBT group compared to 17% in the group receiving treatment as usual (TAU) [17]. However, length of treatment during this trial was comparable to psychotherapeutic interventions such as DBT-A. Treatment of NSSI is indispensable and, therefore, there is a great need for specific and effective psychotherapeutic treatment programs for adolescent NSSI. Such a program should focus on NSSI itself and needs to be time and cost efficient [18]. It should aim to reduce distress and impairment associated with negative emotional states in young people so as to decrease subsequent NSSI [16].

Evans *et al*. [19] at Kings College London, UK, developed a short-term therapy for adults with deliberate self-harm (DSH, which includes suicidal behavior and NSSI). This cognitive-orientated and problem-focused short-term therapy program, called the ‘Manual-Assisted Cognitive-behavioural Therapy’ (MACT), consists of a maximum of six therapeutic sessions and is assisted by a detailed manual. The content of MACT involves problem finding and solving, advantages and disadvantages of DSH, basic cognitive techniques to manage emotions and negative thinking, finding coping strategies and relapse prevention. In a RCT, the MACT program was tested versus TAU in 36 patients following episodes of DSH. The patients in the TAU group were followed by psychiatrists, social workers, members of the community mental health team or nobody. Most patients in the MACT group had therapeutic sessions conducted by psychiatrists, nurses or social workers, but a few of them (22.2%) only had the booklet, which they worked through by themselves. As a result, attempted suicide, the frequency of self-harm episodes and the number of depressive symptoms were significantly lower in the MACT treatment group than in the TAU group [19].

Taylor *et al*. [20] adapted the MACT for adolescents and tested it in an initial study in England. The adolescent version of the program is called the ‘The Cutting-Down Programme’ (CDP) and consists of 8 to 12 individual therapy sessions. This small pilot study (n = 16), which has recently been published [20], showed significant reductions in self-harming behavior, depressive symptoms and trait anxiety.

### Objectives

The aim of the study is to determine the effectiveness of the German CDP for treatment of NSSI in adolescents as compared to TAU. The main outcome objective of the trial is a clinically significant reduction (or remission) by at least 50% in the frequency of NSSI assessed by the Self-Injurious Thoughts and Behaviors Interview-German (SITBI-G) [21,22]. Secondary outcome criteria are a reduction in symptoms of depression as measured by the Beck Depression Inventory (BDI-II) [23] and an increase in self-reported well-being and self-esteem as measured by the KIDSCREEN [24] and Self-Esteem Scale (SES) [25], respectively. Additionally, comorbid psychiatric disorders and childhood adversity will be evaluated as predictors of therapeutic outcome.

### Primary hypothesis

Significantly more adolescents in the CDP group than in the TAU group will experience a clinically significant reduction in the frequency of non-suicidal self-injurious behaviors.

## Methods/Design

### Setting and recruitment

The trial is a single-center RCT performed at the Clinic of Child and Adolescent Psychiatry at the University Hospital of Heidelberg, Germany. The study protocol was approved by the ethics committee of the medical faculty at the University of Heidelberg. In all, 80 adolescents from across the geographical area of the city of Heidelberg between 12 and 17 years of age will be recruited. The potential participants and their families will be approached through our own in- and outpatient units, official notices posted in the surgical and the pediatric clinics, newspaper articles, advertisements on the clinic’s web page, and the study flyer. Adolescents will be initially screened via telephone to determine eligibility and to provide detailed information about the study.

### Inclusion and exclusion criteria

Boys and girls between 12 and 17 years of age who have engaged in at least five prior acts of cutting, burning, stabbing, hitting, excessive rubbing, and similar injuries during the past 6 months will be included. The last NSSI must have occurred within the month previous to the time of screening for the study. All adolescents are required to provide written informed consent to participate in the study, and for those under 16 years of age, written consent also must be provided by the parents/caregivers/legal substitute. Acute psychotic symptoms and acute intent to harm self or others, which requires immediate, intensive psychiatric intervention, constitute exclusion criteria. Other exclusion critieria are impaired intellectual functioning (according to clinical evaluation by a psychologist, whereby only adolescents who attend a regular school were assessed) and being in psychotherapy at the beginning of the study or already having completed NSSI therapy.

### Procedure and randomization

After obtaining informed and written consent according to the approved ethics committee’s protocol, an appointment for the baseline assessment will be set. The baseline assessment will take place at the Clinic of Child and Adolescent Psychiatry and will be performed by a clinical psychologist blinded to the group affiliation. In the baseline assessment, a broad range of psychological measures will be administered (see assessment). After eligibility is confirmed during baseline assessment, adolescents will be enrolled in the trial and will be randomly assigned to one of the two treatment groups as a baseline adaptive randomization. Each participant will be informed about the result of the randomization via telephone within seven days after their baseline assessment. Within the following days, the adolescents will receive a contact card, which is adapted according to the treatment group they are allocated to. Participants who are in the CDP group will promptly receive 8 to 12 weekly individual psychotherapy sessions. Participants in the TAU group will be referred to the public mental health care system. A special cooperation has been set up with the health care system to ensure that the participants will receive the first appointment there within the following 2 to 4 weeks. After completion of the CDP, the post-treatment assessment will be conducted immediately, which is approximately 4 months after baseline assessment. In order to match the assessment points between groups, TAU participants will be invited to their post-treatment assessment 4 months after the baseline. The follow-up assessment will take place 6 months after the post-treatment assessment for every participant. The timeframe of the trial is approximately 10 months for each of the participants, regardless of the treatment group. Figure 1 gives an overview of the trial procedure.

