### Sample size

With an expected response rate of 25% in TAU and 60% in CDP, a sample size of 40 for each group is needed to achieve sufficient power (85%).

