### Statistical analysis

To ensure objectivity of the data collection setting the whole process has been standardized. Data collection and treatment will be strictly separated and performed by different personnel (blinded). The data collection process comprises the baseline, the post-treatment and the follow-up assessment. All analyses will be intent-to-treat analyses. If post-treatment or follow-up assessments are missing, the missing assessment will be filled with the last non-missing value. NSSI, which is the main outcome of this trial, will be assessed using the SITBI-G. A clinically significant improvement is defined as a reduction in the frequency of NSSI by 50%. In this process the TAU group and the CDP group will be compared with each other to determine any differences in primary and secondary outcomes by using a *χ*^2^ - test. As a secondary measure, ANCOVA with group as factor and frequency of NSSI at baseline as covariate will be assessed. Explorative analysis will be executed to account for the influence of childhood trauma, psychiatric diagnosis and personality traits and other factors potentially influencing the patients (for example, gender). Descriptive analysis will be used to characterize the study sample. For nominal data frequencies will be determined, and for continuous data means and standard deviations with confidence intervals will be calculated. A significance level of α = .05 will be chosen. Statistical analysis will be performed using Stata 13.

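### Allocation is baseline-adaptive but the primary chi-square test uses none of the balancing factors: conservative and slightly less powerful if those factors predict response

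*Protocol article*

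**What the plan says.** Under Procedure and randomization, the protocol article states that participants "will be randomly assigned to one of the two treatment groups as a baseline adaptive randomization". The article does not list the baseline characteristics that drive the allocation.

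Under Statistical analysis, the primary endpoint is binary: "A clinically significant improvement is defined as a reduction in the frequency of NSSI by 50" percent. The two groups "will be compared with each other to determine any differences in primary and secondary outcomes by using a" chi-square test. No strata or covariates are attached to it.

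The same section puts adjustment elsewhere: "As a secondary measure, ANCOVA with group as factor and frequency of NSSI at baseline as covariate will be assessed". Other patient characteristics are left to exploratory work: "Explorative analysis will be executed to account for the influence of childhood trauma, psychiatric diagnosis and personality traits", with gender given as a further example.

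Under Sample size, the design rests on an unadjusted comparison of two proportions, "With an expected response rate of 25% in TAU and 60% in CDP", with 40 per group for 85% power.

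**The concern.** Baseline-adaptive allocation makes the arms more alike on the chosen factors than simple randomisation would. The ordinary chi-square test takes its variance from the pooled response rate alone, as if those factors could still differ between arms by chance. If they predict response, that variance is too large for the design used. The p-value then tends to be too large, an unadjusted confidence interval too wide, and the actual type I error falls below the nominal 5%. Some of the benefit of balancing is not carried into the test.

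At stake is a modest amount of power and an accurate significance level in a trial of 80 patients. The remedy needs no new data, because factors used in the allocation must be known before assignment.

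**Working it through.** **Inputs from the article.** Response 25% (TAU) and 60% (CDP), 40 per group, power 85% (Sample size); alpha 0.05 (Statistical analysis). Two-sided testing is assumed, because the article does not state sidedness.

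**Assumptions not in the article.** Two independent binary balancing factors, each present in half the patients and each with the same odds ratio (OR) for response. The simulations use minimisation with a biased coin of 0.8.

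**1. The plan's own figure.** With d = 0.35 and pooled rate 0.425:
- Uncorrected: n = [1.960·√(2·0.425·0.575) + 1.036·√(0.25·0.75 + 0.60·0.40)]² / 0.35² = (1.370 + 0.678)² / 0.1225 = 34.2, so 35 per group.
- With continuity correction: (34.2/4)·[1 + √(1 + 4/(34.2·0.35))]² = 39.7, so 40 per group. The stated size is reproduced.
- Power at 40 per group, no balancing effect: the null standard error is √(0.48875/40) = 0.1105 and the alternative standard error is √(0.4275/40) = 0.1034. Uncorrected power is Φ[(0.35 − 1.960·0.1105)/0.1034] = Φ(1.29) = 90.1%. Subtracting 1/40 from d for the correction gives Φ(1.05) = 85.3%.

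**2. Type I error of the unadjusted test when the strata are balanced.** Let R² be the share of response variance explained by the strata at a 25% rate. The true variance of the difference is (1 − R²) times the one the chi-square test uses, so the actual level is 2·[1 − Φ(1.960/√(1 − R²))].
- OR 2: R² = 0.042, level 0.045.
- OR 3: R² = 0.098; 1.960/√0.902 = 2.064, level 0.039.
- OR 5: R² = 0.185; 1.960/√0.815 = 2.171, level 0.030.
- OR 8: R² = 0.272, level 0.022.

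**3. Power by the same approximation, 25% against 60%.** At OR 3 the true standard error is 0.0975. The null standard error is 0.1105 unadjusted and 0.1052 within strata.
- Unadjusted: Φ[(0.35 − 1.960·0.1105)/0.0975] = 91.4%.
- Stratified: Φ[(0.35 − 1.960·0.1052)/0.0975] = 93.0%.
- At OR 2 the figures are 90.7% and 91.4%; at OR 8 they are 93.7% and 96.7%.

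**4. Simulation with n = 80**, uncorrected chi-square against Cochran-Mantel-Haenszel (CMH):

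| OR per factor | Type I error, chi-square | Power, chi-square | Power, CMH |
|---|---|---|---|
| 1 | 5.2% | 90.4% | 89.5% |
| 2 | 5.3% | 91.8% | 91.0% |
| 3 | 4.3% | 91.6% | 92.2% |
| 5 | 2.8% | 92.9% | 94.9% |
| 8 | 2.9% | 94.3% | 96.9% |

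CMH held its level across the simulations, at about 4.3% to 5.6%. At OR 1 and 2 there is no clear gain from stratifying, and CMH can be up to about a point lower in power.

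**5. Not every adjusted test holds its level at this size.** The logistic likelihood-ratio test ran at 5.6% to 6.6%. A logistic model with log baseline NSSI frequency added, tested by a model-based Wald test of the standardised risk difference, ran at 6.0% to 6.9%.

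**The case against.** The strongest reply is that the named test errs on the safe side and still meets its target. That stands. A reader might infer that ignoring the adaptive allocation inflates type I error or leaves the trial underpowered. The documents do not support either: the effect runs the other way, and at the planned rates unadjusted power is at least 90% uncorrected and at least 85% with continuity correction in every setting computed.

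Second, the balancing factors are unnamed, so a loss cannot be asserted outright. This also stands: the effect is conditional, and the larger deviations need strong factors for which the article gives no evidence. The missing list is not itself a fault, since a condensed article may leave it to the full protocol or the SAP. The test, however, is named in the article, and nothing there brings the allocation factors into it.

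Third, baseline NSSI frequency is already handled. That is largely right. A reader might infer that leaving it out of the primary test is a defect in its own right. But each patient's 50% reduction is measured against that patient's own baseline, and the secondary ANCOVA adjusts for it. The ANCOVA is not the primary test, though, and is not said to include the balancing factors, so it does not answer the main point.

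**Conclusion.** The mismatch is real: allocation uses baseline factors and the primary test does not. Its consequence is conditional and small. Under the assumption of two binary factors at the planned 25% against 60%, the chi-square test runs at about 5%, 4% and 3% for odds ratios of 2, 3 and 5 per factor, and gives up about 0 to 2 points of power against a stratified test. With odds ratios as extreme as 8, the loss is about 3 points. If the factors do not predict response, the two tests are practically equivalent. The 40 per group and the 85% power remain valid. This is a worthwhile improvement, not a threat to the trial's validity.

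**What to change.** In Statistical analysis, specify that the primary test of the 50% responder endpoint is adjusted for the few factors used in the adaptive allocation, by a method that holds its level at n = 80. A CMH test with a stratified risk difference and 95% confidence interval would serve. Keep the unadjusted chi-square test as a supporting analysis. Adding baseline NSSI frequency to the primary test is optional unless it is one of the balancing factors; the secondary ANCOVA can stay as planned.

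The cost is a wording change and slightly more analysis work. Trial status reports 22 participants randomised of the planned 80, so the choice can still be fixed well before the results. The downsides are sparse strata if many factors were used in the allocation, and a negligible loss of power (90.4% against 89.5% in the simulation) if the factors turn out not to be prognostic.

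### The post-treatment visit is timed by the end of therapy in CDP but by the calendar in TAU, and the stated session schedule does not reach the stated 4 months

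*Protocol article*

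**What the plan says.** All the timing rules stand in the protocol article under Procedure and randomization.

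- **CDP, post-treatment visit:** "After completion of the CDP, the post-treatment assessment will be conducted immediately, which is approximately 4 months after baseline assessment".
- **CDP, course of therapy:** "Participants who are in the CDP group will promptly receive 8 to 12 weekly individual psychotherapy sessions".
- **TAU, post-treatment visit:** "In order to match the assessment points between groups, TAU participants will be invited to their post-treatment assessment 4 months after the baseline".
- **Notice of allocation, both arms:** "Each participant will be informed about the result of the randomization via telephone within seven days after their baseline assessment".
- **TAU, start of care:** "participants will receive the first appointment there within the following 2 to 4 weeks".
- **Follow-up, both arms:** 6 months from the participant's own post-treatment visit.
- **Overall duration:** "The timeframe of the trial is approximately 10 months for each of the participants, regardless of the treatment group".

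Under Statistical analysis, the main outcome is a 50% reduction in the frequency of non-suicidal self-injury. All analyses are by intention to treat, and missing assessments are replaced by the latest available value.

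**The concern.** The CDP visit is set by an event that happens after randomisation and exists in one arm only. The TAU visit is set by a date. The two coincide only if CDP really ends at 4 months, and a course of 8 to 12 weekly sessions that starts promptly looks too short for that. Because follow-up is counted from the post-treatment visit, any mismatch is passed on to the second visit.

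The outcome is a change from baseline in the frequency of an episodic behaviour, which can shift with time whatever the treatment. If the arms are seen at different times since baseline, the contrast mixes the effect of treatment with the effect of elapsed time. If the CDP visit date also varies with the number of sessions and with attendance, that mixture differs from one CDP participant to the next.

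**Working it through.** **The plan's own figures.** For TAU, 4 months to the post-treatment visit plus 6 months to follow-up gives 10 months, as stated. For CDP, the 4 months has to come out of the session schedule, so that is what was checked.

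**Inputs.** The article gives the number of sessions (k = 8 to 12), weekly spacing, notice of allocation within 7 days, and a prompt start. It gives no week for the first session. I assume s = 1 to 2 weeks after baseline: up to a week for the notice, then a prompt start. One month is 365.25/12/7 = 4.348 weeks, so 4 months is 17.39 weeks.

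**Formulas.**
- Week of the last session = s + (k − 1)
- Gap to the TAU visit = 17.39 − week of the last session
- CDP follow-up in months = (week of the last session)/4.348 + 6

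| Sessions k | First session s (week) | Last session (week) | In months | Weeks before TAU visit | CDP follow-up (months) |
|---|---|---|---|---|---|
| 8 | 1 | 8 | 1.84 | 9.4 | 7.8 |
| 8 | 2 | 9 | 2.07 | 8.4 | 8.1 |
| 12 | 1 | 12 | 2.76 | 5.4 | 8.8 |
| 12 | 2 | 13 | 2.99 | 4.4 | 9.0 |

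**Range over the assumption.** With s from 0 to 4 weeks, the gap runs from 17.39 − 15 = 2.4 weeks (12 sessions, s = 4) to 17.39 − 7 = 10.4 weeks (8 sessions, s = 0). It does not close within this range.

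**What would close it.** The wait before the first session plus missed weeks would have to total 17.39 − (k − 1):
- 12 sessions: 17.39 − 11 = 6.4 weeks
- 8 sessions: 17.39 − 7 = 10.4 weeks

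**Can a gap of this length matter?** This is an illustration only. Take the 25% TAU response rate from the Sample size section, and assume that it is reached at 4 months through a constant hazard: h = −ln(0.75)/4 = 0.0719 per month. Response would then be 1 − exp(−2h) = 13% at 2 months and 1 − exp(−3h) = 19% at 3 months. Visit time can therefore move a responder rate. This is not an estimate of bias in the trial, because the true time course is not known. Assessing on the day that therapy ends could also catch the CDP effect at its largest, which would act in the opposite direction.

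**The case against.** **The authors meant the visits to match.** The article says so: the TAU date was chosen for that purpose, and about 10 months is stated for everyone. Real courses of weekly therapy slip, and the article gives no attendance figures. If enough weeks are lost, the average gap is small. This stands, so a reader who infers that the arms will certainly be compared at different times goes further than the text. What remains is that the slack needed is nowhere mentioned and sits badly with a prompt start and weekly sessions. Equal averages would also leave the individual CDP dates dependent on attendance.

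**Assessing at the end of therapy is a recognised choice in psychotherapy trials.** That is true. It does not, however, give the common 4 and 10 months that the article also claims.

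Three stronger readings are tempting, and the document does not support them:

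- **A large spurious difference in responder rates.** This needs raw counts since baseline, unadjusted for exposure, set against a baseline count over a longer window. The article states no counting window, and the 6 months in the inclusion criteria is an eligibility look-back. Monthly rates or equal windows would remove the systematic exposure effect. At follow-up, a count since the previous visit would cover 6 months in both arms.
- **CDP participants who stop early end up imputed.** Nothing says that they are not assessed, and the full protocol may say when they are. If one did miss the post-treatment visit, carrying baseline forward would record no reduction. That is a possible consequence and no more.
- **Visit timing unblinds the assessor.** The Staff section says that the assessor is blinded and that data collection is separate from therapy. Nothing says that the assessor arranges the visits or knows the time elapsed. This too is only possible.

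**Conclusion.** The point holds as an internal contradiction and a weak timing rule. On the schedule as written, with the first session assumed 1 to 2 weeks after baseline, the CDP post-treatment visit falls about 4 to 9 weeks before the TAU visit. The follow-up visit is then early by the same interval. The stated 4 and 10 months hold in CDP only with about 6 to 10 weeks of start delay and missed weeks combined.

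Whatever the average gap, the visit time is fixed in one arm and depends on post-randomisation behaviour in the other. The contrast on the 50% reduction endpoint may be biased as a result. Neither the direction nor the size can be settled from the article, because the counting window, the time course of the behaviour and the actual session slippage are not given. No figure for the bias should be quoted.

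**What to change.** 1. Reconcile the stated course of sessions with the stated visit times. This review takes no view on the number or pace of sessions.
2. Schedule both post-baseline assessments from one origin, baseline or randomisation, at the 4 and 10 months that the article already names, with the same visit window in both arms.
3. Apply this to every randomised participant, whether or not CDP is completed, and drop completion of therapy as the trigger.
4. Report the actual time from baseline to each assessment by arm, including for participants already assessed under the present rule.

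The cost is a wording amendment and a scheduling rule. Treatment does not change, and the planned 40 per group is not affected. The small downside is that some CDP participants are seen some weeks after their last session and not on that day. According to Trial status, 22 of 80 participants had been randomised, so the 80 − 22 = 58 still to come could all be scheduled under the common rule.
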